## **METHODS**

### **Study design**

The study will be designed as a cross-sectional cohort design with prospective enrolment of patients with SpA over time. Information about the patients and their exposures will be collected at a single center at one visit (figure 2) according to the clinical standards in Denmark. Examinations will be carried out on the same day. Participant inclusion is expected to begin during 2016.

### **Participants**

Patients with any disease of the SpA spectrum seen in the Department of Rheumatology, Odense University Hospital, Svendborg/Odense will be recruited. To be considered for inclusion, participants must have the ability and willingness to give written informed consent and to meet the requirements of this protocol. Participants must be at least 18 years of age. Participants will be excluded from the study if any of the following criteria are present: (1) no consent, (2) does not understand Danish, (3) age < 18 years.

All subjects will be informed about the project's purpose and content both oral and written - as per the Research Ethics Committee. Participants will receive information by MD [name]. Patients are made aware of the possibility to bring one accompanying person. The interview will take place in an undisturbed space at the rheumatology clinic. The subjects were informed that they could at any time withdraw their commitment to participate in the project, without this will affect the current or subsequent treatment or control. The subjects give permission to the investigator to have direct access to source data / documents (including DANBIO) for the monitoring, auditing and / or inspection

by the Research Ethics Committee or the Data Protection Agency. On the consent form, the investigator signing that written and oral information is given as above.

### **Variables and outcome measures**

Included patients will undergo an examination programme to collect variables shown in **table 1**.

Informations on: (1) demographic data (age, sex, height, weight, educational level), (2) clinical characteristics (symptom duration, duration since SpA diagnosis, and type of the form of clinical involvement, HLA-B27, family history and extra-articular manifestations (3) activity data and monitoring methods (erythrocyte sedimentation rate (ESR), CRP, visual analogue scale (VAS) for pain and activity, morning stiffness, joint assessment, painful entheses [BASDAI]), (4) employment status and functional ability [BASFI]) and SF-36 (5) comorbidity will be obtained by interview.

The BASFI is a 10-item scale on which respondents rate the degree of difficulty they have in performing certain tasks, using visual analogue scales (VAS) from 0 (easy) to 100 (impossible). The mean of the 10 responses is the BASFI score. The BASDAI is a 6-item scale to measure severity of fatigue, spinal and peripheral joint pain, localized tenderness and morning stiffness, using the VAS scale as well. The Medical Outcomes Study SF-36 is a generic health status questionnaire that was developed as a tool to compare various aspects of health status across a general and broad patient population (32-34). The SF-36 examines eight general health domains: physical functioning, role limitations due to physical health problems, bodily pain, general health perceptions, vitality, social functioning, role limitations due to emotional problems and mental health. Furthermore, a physical and mental component summary score can be calculated. We will use the Danish version of SF-36 (35) which uses a 4-week recall period. For Peripheral articular involvement 44 tender/swollen joint count will be assessed.

**Table 1** Summary of measures to be collected

|                                                                      |   |
|----------------------------------------------------------------------|---|
| Demographics                                                  | X |
| Sex (M/F)                                                            | X |
| Age (year)                                                           | X |
| Height (cm)                                                          | X |
| Weight (Kg)                                                          | X |
| BMI (Kg/m  )                                             | X |
| Disease Characteristics                                       |   |
| Symptom duration (months)                                            | X |
| Axial disease (yes/no)                                               | X |
| MRI positive (yes/no)                                                |   |
| Peripheral joint involvement (yes/no)                                | X |
| Medication                                                    |   |
| Prior NSAID (yes/no)                                                 | X |
| Current NSAID at assessment (yes/no)                                 | X |
| Prior DMARD therapy (yes/no)                                         | X |
| MTX dose (mg/week)                                                   | X |
| Other current DMARD therapy                                          | X |
| No. of previous biologics used (if any)                              | X |
| Name of current biological agent                                     | X |
| Dose of prednisolone orally at assessment (mg/week)                  | X |
| Intramuscular glucocorticoid injections in the previous 3 month (mg) | X |
| Clinical examination                                          |   |
| 46 swollen joint count                                               | X |
| 46 tender joint count                                                | X |
| BASMI                                                                | X |
| SpA features                                                  |   |
| Anterior uveitis, past or present (yes/no)                           | X |
| Inflammatory bowel disease, past or present (yes/no)                 | X |
| Psoriasis, past or present (yes/no)                                  | X |
| Preceding infection (yes/no)                                         | X |
| Total enthesitis count                                               | X |
| Dactylitis count                                                     | X |

|                                                                                                                                                                                                                   |   |
|-------------------------------------------------------------------------------------------------------------------------------------------------------------------------------------------------------------------|---|
| Co-morbidities                                                                                                                                                                                             |   |
| Charlson Comorbidity Index                                                                                                                                                                                        | X |
| Urine sample                                                                                                                                                                                               | X |
| Basic metabolic screening                                                                                                                                                                                         | X |
| S-creatinin                                                                                                                                                                                                       | X |
| S-ioniseret calcium                                                                                                                                                                                               | X |
| S-urat                                                                                                                                                                                                            | X |
| Urine-pH (dip-stick)                                                                                                                                                                                              | X |
| Urine Calcium                                                                                                                                                                                                     | X |
| Urine Chloride                                                                                                                                                                                                    | X |
| Urine Potassium                                                                                                                                                                                                   | X |
| Urine Sodium                                                                                                                                                                                                      | X |
| Urine Creatinin                                                                                                                                                                                                   | X |
| Urine albumin                                                                                                                                                                                                     | X |
| Urine Oxalate                                                                                                                                                                                                     | X |
| Patient-reported outcomes                                                                                                                                                                                  |   |
| BASDAI                                                                                                                                                                                                            | X |
| BASFI                                                                                                                                                                                                             | X |
| SF-36                                                                                                                                                                                                             | X |
| Blood samples                                                                                                                                                                                              |   |
| *HLA-B27 (positive/negative)                                                                                                                                                                                      | X |
| **CRP, ESR, vitamin D, immunoglobulin A, ALAT, alkaline phosphatase, creatinine, estimated GFR, haemoglobin, erythrocyte volume fraction, MCHC, MCV, leucocytes, differential count, thrombocytes, P-calprotectin | X |
| Stool sample                                                                                                                                                                                               |   |
| Faecal calprotectin (mg/L)                                                                                                                                                                                        | X |

\*will not be repeated if already taken

\*\*will not be repeated if taken within the past 2 weeks

CRP, C-reactive protein; ESR, erythrocyte sedimentation rate; ALAT, alanine transaminase; GFR, glomerular filtration rate; MCHC, mean corpuscular

haemoglobin concentration; MCV, mean corpuscular volume; MTX; methotrexate, DMARD; disease-modifying antirheumatic drugs

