### **Rationale and hypothesis**

In AS first line of therapy is NSAID, but in patients with simultaneous IBD these should be administered with caution as some studies have suggested that they exacerbate intestinal inflammation (19). Early induction of an anti-TNF therapy among these patients is recommended(20). Furthermore enthesitis is a typical feature in SpA and the treatment of these manifestations seem to be challenging as well. Studies have showed that anti-TNF therapy is superior to conventional DMARD in patients with longstanding enthesitis (21, 22). Uveitis is an acute inflammation of the uvea and is a common and potential serious extra-articular manifestation in patients with SpA. In most cases acute uveitis can be successfully treated by the ophthalmologists with local corticosteroids, but in some cases it develops into a refractory uveitis, and treatment with TNFi is recommended (as azathioprine and methotrexate do not have sufficient effect on the disease activity of SpA) (23, 24).

We anticipate that extra-articulare manifestations among patients with SpA is

underestimated and therefore undertreated, and contributes to a reduced quality of life. Spondyloarthritic disorders are generally diagnosed more often in men than in women (25). In reference to the most representative form of these disorders, ankylosing spondylitis, three male cases are documented for every female case (25). However, since the introduction of the new ASAS criteria for axial spondyloarthropathies these differences are no longer so apparent (26). SpA appears to be more frequent in men than in women, particularly in its axial presentations (27). Nevertheless, little is known of the differential clinical expression of SpA between males and females. The explanation for these differences is not clear, and the participation of multifactorial parameters cannot be discarded. A few studies have analysed gender as a prognostic factor of the SpA (8-10) and there is a need to determine the particularities and severity of SpA in the female gender. We hypothesise that the amount of self-reported disease activity is more pronounced in woman than in men. (i.e. Bath Ankylosing Spondylitis Disease Activity Index (BASDAI (28)) and Bath Ankylosing Spondylitis Functional Index (BASFI (29)). As it seems to be a link between IBD and SpA, we also aimed to measure faecal calprotectin in patients with any disease within the SpA spectrum.

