## **Aims**

1. To analyze the distribution according to specific concomitant conditions in the SpA group:

Ankylosing spondylitis was diagnosed when the patients fulfilled the modified New York criteria (30), psoriatic arthritis was diagnosed when patients fulfilled the CASPAR criteria (31), enteropathic arthritis was diagnosed when patients exhibited inflammatory axial and/or peripheral

joint involvement associated to a confirmed IBD (Crohn's disease or ulcerative colitis), SpA was diagnosed when patients fulfilled the ASAS criteria (2), reactive arthritis was diagnosed when an asymmetric inflammatory oligoarthritis and/or inflammatory low back pain associated to confirmed genitourinary or gastrointestinal tract.

2. To characterize the extra-articular manifestations according to ASAS criteria, however also including the recently described nephrolithiasis among SpA patients:  
Anterior uveitis, (past or present), inflammatory bowel disease (past or present) enthesitis (past or present), psoriasis (past or present) dactylitis (past or present) and furthermore to assess other features as: urethritis, pyoderma gangrenosum, keratoderma blennorrhagica, erythema nodosum (past or present), nephrolithiasis (past or present), and urine components.
3. To estimate the male-to-female ratio among patients with SpA
4. To investigate faecal calprotectin in patients with any disease in the SpA spectrum
5. To analyze the influence of gender on self-reported disease activity:  
Estimation of disease activity and functional status is evaluated using BASDAI, BASFI and 36-Item Short-Form Health Survey (SF-36)
6. To analyze co-morbidity among SpA patients using Charlson Comorbidity Index

A priori hypotheses are as follows:

- A. The amount of self-reported disease activity is more pronounced in woman than in men

- B. Females are more likely to have peripheral joint involvement rather than axial compared to men
- C. Extra articular manifestations are more frequent seen in males compared with females
- D. Faecal calprotectin is higher in men than women
- E. Urine electrolytes are altered and related to nephrolithiasis and NSAID exposure

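### Hypothesis E concerns NSAID exposure, but Table 1 records NSAID use only as yes/no flags, so it cannot support a dose or duration relation and may pool occasional with daily users

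*Protocol*

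**What the plan says.** The protocol's Aims section lists five a priori hypotheses. The last, E, reads "Urine electrolytes are altered and related to nephrolithiasis and NSAID exposure". It is the only one of the five that names a drug.

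The Medication block of Table 1 (Variables and outcome measures) holds two NSAID items: "Prior NSAID (yes/no" and "Current NSAID at assessment (yes/no". Neither carries an agent, an amount, a number of days or a look-back period, and the text around the table adds nothing on NSAIDs.

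The same block asks for quantities of other drugs: "MTX dose (mg/week", "Dose of prednisolone orally at assessment (mg/week" and "Intramuscular glucocorticoid injections in the previous 3 month (mg". The last of these also has a time window.

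Rationale and hypothesis gives some background on use: "In AS first line of therapy is NSAID", but "in patients with simultaneous IBD these should be administered with caution". Study design fixes one visit, with all examinations on the same day. Participants admits the whole SpA spectrum, not AS alone.

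**The concern.** The one drug exposure that a hypothesis depends on is measured more coarsely than three drugs that no hypothesis mentions. A urine sample taken at the visit should mainly reflect recent use and how much was taken. The current-use flag captures recency roughly and amount not at all. If the current group combines people who take an NSAID now and then with people who take it daily, any effect confined to regular users is averaged down, and a null result for Hypothesis E becomes hard to interpret.

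This is a matter of data collection. A statistical analysis plan can choose groupings and models, but it cannot create doses or days of use that nobody asked about, and the protocol plans no second contact at which to ask.

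**Working it through.** **1. The protocol's own figure.** Sample size considerations gives a two-sample pooled t test, two-sided 0.05, SD 1.5, difference 1 BASDAI unit, 100 patients split 1:1, power 91%.

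- Standardised difference d = 1/1.5 = 0.667.
- Noncentrality = d / √(1/n₁ + 1/n₂) = 0.667 / √(1/50 + 1/50) = 0.667/0.2 = 3.33.
- Critical value of t on 98 df = 1.984.
- Power = 91.0%.

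The stated figure reproduces. It belongs to Hypothesis A (BASDAI by sex). The protocol states no power for Hypothesis E.

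**2. Assumed inputs for Hypothesis E.** The documents give no NSAID prevalence, no pattern of use and no expected effect on a urine measure. All of the following are therefore assumptions:

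- n = 100, with 50 current users and 50 others;
- a true effect of 0.65 SD on a urine measure, chosen to give about 90% power when every current user carries the effect;
- only a fraction f of current users (the regular takers) carries the effect, and the rest carry none.

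The expected difference between the two flag groups is then f × 0.65 SD, and the noncentrality is f × 0.65/0.2.

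| f | Difference (SD) | Noncentrality | Power |
|---|---|---|---|
| 1 | 0.65 | 3.25 | 0.896 |
| 0.75 | 0.4875 | 2.4375 | 0.675 |
| 0.50 | 0.325 | 1.625 | 0.363 |
| 0.25 | 0.1625 | 0.8125 | 0.127 |

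**3. Sensitivity to the method.** A mixed group is also more variable: its variance becomes 1 + f(1−f)d². With this included and the protocol's d = 0.667 carried over, power at 50:50 is 91%, 68%, 36% and 12.5% for the same four values of f. At a 70:30 split of users to non-users it is 86%, 60%, 31% and 11%. The pattern does not depend on the exact effect size or on ignoring the extra variance.

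**4. The prior-use flag.** Here the question is imbalance. With d = 0.667 and no mixing, power by ever-users to never-users is 91% at 50:50, 75% at 80:20, 51% at 90:10 and 30% at 95:5. Contrast nearly vanishes only at about 95% ever-use or more. The documents do not say where the cohort will lie.

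**The case against.** The strongest reply is that Hypothesis E speaks of a relation with exposure, not with dose or duration. A yes/no exposure is a crude but legitimate measure of that. The two flags combine into never, past and current, and current against not current is the natural contrast for a same-day urine sample. The protocol calls the study exploratory. Table 1 is a summary of measures, and it omits dose for some other drugs too: other DMARDs and biological agents have no dose item. All of this stands, and it limits the point to an improvement in measurement.

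A reader might infer more than the documents support:

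- **That prior use will hardly vary.** First-line status is stated for AS only. The cohort covers the whole SpA spectrum, and the protocol advises caution with NSAIDs in patients with IBD. Nothing says that Hypothesis E will be tested on prior use.
- **That the current group is heavily mixed.** The protocol neither defines current use nor describes its pattern, so mixing is possible but not established.
- **That recent exposure goes unrecorded.** It is recorded, as current use at assessment. What is missing is the amount and the number of days.
- **That a null result would carry no information.** At f = 0.75 power is still 67% under the assumptions above. A null would be harder to read, but not empty.

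What the reply does not answer is that never, past and current still leave no gradation within the current group, the group most relevant to the urine sample.

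**Conclusion.** The point holds as a mismatch between a stated hypothesis and the data collected for it. The flags cannot support any dose or duration relation for Hypothesis E, and they may pool occasional with daily users. Neither limitation can be repaired after the single visit.

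The size is conditional. If current users all take NSAIDs regularly, nothing is lost for a simple current-against-not contrast. If only half of them carry the effect, power falls from 90% to 36%, given 100 patients, an even split and an effect of 0.65 SD, all assumed. One a priori hypothesis of an exploratory study is affected. The BASDAI comparison and its 91% power are untouched.

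**What to change.** Keep both flags in Table 1. For current users, add the NSAID name, the daily dose, and the number of days taken in the 7 days before the urine sample (0 to 7). State that Hypothesis E uses days of recent use as its exposure, with current use yes/no as a secondary contrast. The 7-day window is a proposal, chosen because the urine sample should mainly reflect recent use; the documents do not supply one.

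The cost is two or three extra questions in an interview that already takes place, with no extra test. Self-reported days carry some recall error. Doses of different NSAIDs need a common scale before they are pooled, which is why days of use is the simpler main exposure.

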**Method and analysis:**

We anticipate that we will be able to enroll 100 adult individuals ( $\geq 18$  years of age) diagnosed with SpA. Among these individuals we want to explore the prevalence of concomitant extra articular manifestations. Data (duration of illness, diagnostic category, disease activity, extra-articular manifestations, blood, urine, and faeces samples, patient reported outcomes and comorbidity) will be collected from each participant. For all the clinical characteristics we will explore whether any of these have an impact on the reported disease activity according to the international standards – the Bath Ankylosing Spondylitis Disease Activity Index

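### One lifetime yes/no item each for uveitis, IBD and psoriasis suits the prevalence aim but blurs the planned exploration against BASDAI at the visit

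*Protocol*

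**What the plan says.** In the protocol, Table 1 (Variables and outcome measures, under SpA features) gives each of three manifestations a single field: "Anterior uveitis, past or present (yes/no"), "Inflammatory bowel disease, past or present (yes/no") and "Psoriasis, past or present (yes/no"). No date, current-activity or severity field is listed for any of them. In the same block enthesitis is recorded differently, as "Total enthesitis count", and dactylitis is also a count. In the medication block, earlier NSAID use and NSAID use at the assessment are two separate items.

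The fields are put to more than one use:

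- Aim 2 is "To characterize the extra-articular manifestations according to ASAS criteria", and it repeats the past-or-present wording for these conditions.
- Hypothesis C compares the frequency of manifestations between men and women.
- The abstract (Method and analysis) says "we want to explore the prevalence of concomitant extra articular manifestations", and then "For all the clinical characteristics we will explore whether any of these have an impact on the reported disease activity", with BASDAI named as the measure.

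Study design states that everything is collected at one visit. Rationale and hypothesis adds an expectation that these manifestations are "underestimated and therefore undertreated, and contributes to a reduced quality of life".

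**The concern.** The time window of the exposure does not match that of the outcome. BASDAI describes the patient at the one study visit, and SF-36 looks back 4 weeks. The manifestation fields look back over a lifetime. A patient with a single uveitis attack many years ago and a patient with active uveitis at the visit are both coded yes.

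If it is mainly active disease that goes with a higher BASDAI, the comparison of yes with no mixes affected and unaffected patients in the yes group, and the observed difference shrinks. A null result could then be reported as no impact when the contrast was simply diluted. The distinction has to be collected at the visit. No later analysis of the listed variables can recover it for uveitis or psoriasis.

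**Working it through.** **The protocol's own figure.** Sample size considerations gives 91% power for the male-female BASDAI comparison: two-sided pooled t test at 0.05, SD 1.5, 50 per group, difference 1. The standard error is 1.5 × √(1/50 + 1/50) = 0.300 and the noncentrality is 1/0.300 = 3.33. With 98 degrees of freedom the power is 91.0%. The figure reproduces and is not in dispute. The same method is used below.

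**Inputs.**

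- From the protocol: 100 patients, SD 1.5, two-sided 0.05.
- Assumed, not in the documents: 30 of 100 ever-positive; BASDAI 1 unit higher if the manifestation is active; no shift if it is past only; an active share *a* of the positives, shown as a range.

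**Lifetime item (30 yes against 70 no).** The expected difference is *a* × 1 + (1 − *a*) × 0 = *a*. The standard error is 1.5 × √(1/30 + 1/70) = 0.327. Power follows from the noncentral t with 98 degrees of freedom and noncentrality *a*/0.327.

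**Item for presence at the visit (active against all others).** The number active is 30*a*. Everyone else, including past-only cases, has no shift, so the difference is 1. The standard error is 1.5 × √(1/(30*a*) + 1/(100 − 30*a*)).

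| Active share *a* | Difference, lifetime item | Power, lifetime item | Number active | Standard error, active vs others | Power, active vs others |
|---|---|---|---|---|---|
| 100% | 1.00 | 86% | 30 | 0.327 | 86% |
| 50% | 0.50 | 33% | 15 | 0.420 | 65% |
| 25% | 0.25 | 12% | 7.5 | 0.569 | 41% |
| 10% | 0.10 | 6% | 3 | 0.879 | 20% |

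The 7.5 is an expected count; 7 or 8 patients would give 39% or 43%. The relevant comparison is across each row. The 86% in the first row is not what the added item would deliver, because it arises only if every positive case is active, and then the two codings coincide.

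**Sensitivity to the number ever-positive.** With half of the positives active:

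| Ever-positive of 100 | Power, lifetime item | Power, active vs others |
|---|---|---|
| 10 | 17% | 30% |
| 20 | 26% | 51% |
| 30 | 33% | 65% |
| 40 | 37% | 75% |

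The direction is the same throughout. The separate item does better although its group is smaller, and the absolute power remains modest.

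**The case against.** The strongest reply is that the lifetime definition is a choice, not an oversight. Aim 2 uses the same wording and ties it to the ASAS criteria, and Table 1 collects what Aim 2 asks for on these three conditions. Hypothesis C concerns how frequent the manifestations are by sex, which a lifetime field can answer. Age, symptom duration and time since diagnosis are recorded, so adjustment for length of illness is possible. All of this stands.

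Three stronger readings are tempting and are not supported:

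- A reader might infer that the manifestations cannot be related to BASDAI at all. They can. The estimate then concerns history of the condition and is diluted as a measure of active disease.
- A reader might infer that the study sets out to test undertreatment and cannot. Undertreatment is an expectation stated in the rationale. None of the six aims or Hypotheses A to E tests it. In Aim 5, SF-36 serves the comparison by gender.
- A reader might infer that current state is wholly unobserved. Faecal calprotectin gives some information on current gut inflammation, and current NSAID, DMARD, biological and prednisolone use are listed. Neither shows whether uveitis or psoriasis is active at the visit.

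Two further points have some weight. Table 1 is headed as a summary, so the case record form may hold more detail; the protocol does not say so. The effect of 1 unit is also an assumption, and BASDAI measures fatigue, pain, tenderness and stiffness rather than eye, gut or skin activity, so the true shift could be smaller. That would lower both power columns and would not remove the dilution.

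**Conclusion.** The point holds in a limited form. The three lifetime items are adequate for Aim 2 and Hypothesis C. They do not suit the exploration against BASDAI announced in the abstract, because remote and active disease share one code and the listed variables cannot separate them afterwards, with only partial help from faecal calprotectin for the gut. Under the stated assumptions, the loss at active shares of 50%, 25% and 10% is the gap between 33%, 12% and 6% and about 65%, 41% and 20%.

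The prevalence, the active share, the 1-unit effect and the zero effect of past disease are illustrative and do not come from the documents. The conclusion that dilution occurs needs only that active disease relates to BASDAI more strongly than past disease does, and that some of the positives are past cases. This is a low-cost improvement to an exploratory study. It does not invalidate the aims that the fields were written for.

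**What to change.** Keep the ever (yes/no) item for uveitis, IBD and psoriasis in Table 1, for Aim 2 and Hypothesis C. For each of the three, add present at the visit (yes/no) and year of last episode. State that the present item is used when manifestations are related to BASDAI, BASFI and SF-36. Table 1 already makes this kind of split for NSAID use.

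If the items are not added, state in the protocol that any result relating these manifestations to BASDAI, BASFI or SF-36 concerns lifetime history only, and that a null result does not show that active disease has no impact.

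The cost is a few more questions at the same interview, with no extra visit or test. The groups with a manifestation present will be small and their intervals wide. With 15 active patients of 100, for example, the 95% half-width is about 1.98 × 0.420 = 0.83 BASDAI units. The protocol should say so.
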